##### Frequency of blood lipid and urinary albumin testing

Clinical practice guidelines recommended that blood lipids and urinary albumin levels were tested once every 12 months as part of an annual cycle of care, with re-testing to occur within three months if the result was outside recommended levels [13]. Over each 24-month period, the number of all cases where there was at least one gap between tests of more than 12 months (13 months or greater) was determined and aggregated for each town. For each case with at least one test outside recommended target levels [13], the number of cases where a subsequent gap between tests of more than three months (four months or greater) was determined and aggregated for each town. The mean gap between blood lipid and urinary albumin tests for each case was also determined.

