## Background

Type 2 diabetes is one of the fastest growing chronic diseases internationally [1]. It is estimated that world prevalence of diabetes in adults will rise from 6.4% in 2010 to 7.7% by 2030 [2]. Long-term complications associated with diabetes include macrovascular disease, coronary heart disease, stroke, retinopathy, and kidney diseases [3]. Those diagnosed with diabetes have double the risk of developing cardiovascular disease (CVD) and have a higher mortality due to their first CVD event [3,4]. Diabetic nephropathy affects approximately 10% of people with diabetes, is the most common cause of end-stage kidney disease, and diabetes is a major contributor to lower limb amputations and visual loss [3]. The direct and indirect costs of diabetes and its associated complications to the health system and to individuals is substantial [5].

The health complications associated with type 2 diabetes can be prevented, delayed, or lessened if diabetes is diagnosed early and is well controlled. While there are many factors important to diabetes control, metabolic markers of poor diabetes control such as elevated blood glucose, blood lipids, cholesterol, and urinary albumin indicate increased risk of diabetic complications [6-11]. Interventions designed to impact on multiple risk factors in people with diabetes can reduce risk of diabetes complications [6,12]. However, achieving optimal diabetes management at a population-level remains challenging.

General practitioners (GPs), or primary care physicians, play a major role in diabetes management [3]. In an effort to improve diabetes management, national Clinical Practice Guidelines for general practice specify the requirements for testing of blood lipids, HbA1c, and urinary albumin [6,13]. Target levels for each of these metabolic indicators are provided, and follow-up care is recommended if results fall outside these parameters [13]. While these metabolic markers cannot assess the quality of an individual’s diabetes care, they represent key objective measures of the management of diabetes at a population level. While there were about 818,000 Australians diagnosed with diabetes in 2009 and 2010, it appears that a minority have received the recommended annual testing of metabolic markers [14].

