#### Secondary outcome

##### Frequency of HbA1c testing

NHMRC guidelines [6] recommended HbA1c testing every six months if the result was <7.0%, with re-testing to occur within three months if the result was ≥7.0%. Over each 24-month period, the number of all cases where there was at least one gap between tests of more than six months (seven months or greater) was determined and aggregated for each town. For each case with at least one HbA1c test >7.0%, the number of cases where a subsequent gap between HbA1c tests of more than three months (four months or greater) was determined and aggregated for each town. The mean gap between HbA1c tests for each case was also determined.

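### Testing frequency is scored only through gaps between tests, so cases tested too rarely to have a gap cannot be counted as failing

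*Protocol article*

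**What the plan says.** The testing-frequency outcomes in the protocol article all rest on intervals between successive tests.

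- **Lipids and albumin** (Frequency of blood lipid and urinary albumin testing). The standard is that "blood lipids and urinary albumin levels were tested once every 12 months as part of an annual cycle of care". The measure is "the number of all cases where there was at least one gap between tests of more than 12 months (13 months or greater". After an out-of-target result it is "the number of cases where a subsequent gap between tests of more than three months (four months or greater) was determined". The third measure reads "The mean gap between blood lipid and urinary albumin tests for each case was also determined".
- **HbA1c** (Frequency of HbA1c testing). The measure is "the number of all cases where there was at least one gap between tests of more than six months (seven months or greater". After a result above 7.0% it is "the number of cases where a subsequent gap between HbA1c tests of more than three months (four months or greater) was determined". A mean gap is again computed.

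Three other sections bear on this. Selection of case sample defines a case by HbA1c alone: one result above 7%, or two tests. Data extraction procedure sets 24-month periods before and after the intervention and lists test dates for every marker. Statistical methods analyses the proportion of patients per town with appropriate testing frequency. No sentence covers a case with fewer than two tests, or the time before the first test and after the last.

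**The concern.** Secondary aim 1 asks whether the intervention brings testing up to guideline frequency. The patients furthest from the guideline are those hardly tested, and the stated count cannot register them.

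The case definition admits such patients. Nothing in it requires a lipid or albumin test. It also admits people with a single HbA1c above 7%, who under the guideline the article cites are due a re-test within three months. If they have no further test in the period, they fail neither HbA1c measure.

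The intervention is meant to increase testing. If it moves patients from one test to two widely spaced tests, the count of failures goes up, so better care can be recorded as worse care.

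**Working it through.** **Inputs.** The period is 24 months (Data extraction procedure). The failure limits are 13 months for lipids and albumin, 7 months for HbA1c and 4 months for re-testing (the two frequency sections). The article gives no figure for testing frequency, so there is none to reproduce. Test timing and the distribution of test counts are assumptions below.

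**Step 1: the wording alone.** With no or one test there is no between-test gap, so the case cannot be counted as failing.

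- A case with one lipid test in 24 months is not counted. Add a second test 14 months after the first, and it is.
- A case with an HbA1c above 7% and no later test is not counted on the re-test measure. Re-test that patient at five months, and it is.

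**Step 2: lipids and albumin, by number of tests.** Assume *k* tests at independent uniform times over 24 months. They cut the period into *k* + 1 stretches, and any one of these lasts at least 13 months with probability ((24 − 13)/24)^k = (11/24)^k. Because 13 exceeds half of 24, only one stretch can be that long, so the probabilities add.

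- As written, only the *k* − 1 between-test gaps count: (k − 1)(11/24)^k for *k* ≥ 1.
- With the end stretch also counted: k(11/24)^k.
- With both edge stretches counted: (k + 1)(11/24)^k.
- With no test, the first is 0 and the other two score a failure.

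| Tests in 24 months | As written | End stretch counted | Both edges counted |
|---|---|---|---|
| 0 | 0% | 100% | 100% |
| 1 | 0% | 45.8% | 91.7% |
| 2 | 21.0% | 42.0% | 63.0% |
| 3 | 19.3% | 28.9% | 38.5% |
| 4 | 13.2% | 17.7% | 22.1% |
| 6 | 4.6% | 5.6% | 6.5% |

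As written, no or one test gives the best score and the move to two tests raises failure. From two tests upward the measure moves the right way. Counting the end stretch, or both edges, makes failure fall throughout.

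**Step 3: lipids and albumin, averaged over Poisson test counts.** Let the mean be λ tests per 24 months and x = 11λ/24. Failure as written is e^(−λ)[(x − 1)e^x + 1]; with both edges it is e^(−λ)(x + 1)e^x.

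| λ | As written | Both edges counted |
|---|---|---|
| 0.5 | 1.9% | 94% |
| 1 | 5.3% | 85% |
| 2 | 10.7% | 65% |
| 3 | 12.4% | 47% |
| 6 | 7.0% | 15% |

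For example, at λ = 1, x = 0.458: 0.368 × [(−0.542)(1.581) + 1] = 5.3%. Going from one to two tests on average doubles measured failure while failure with both edges counted falls by 20 points.

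**Step 4: HbA1c.** Under the 7-month limit a single-test case fails with probability 0 and a two-test case with probability (17/24)² = 50%.

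**The case against.** The strongest reply is that the article nowhere says untested patients meet the guideline. It describes a count of long gaps, and Statistical methods does not say that appropriate frequency is simply the complement of that count. A reader might infer that such cases are scored as passes, but that remains an inference. It does not rescue the measure. The article gives an explicit rule, with limits and applied to all cases, so this is not detail left to a fuller document. If an unseen plan instead drops cases with fewer than two tests, the worst-tested patients leave the denominator and the distortion stays.

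A reader might also infer that many cases are affected, because the Background says "it appears that a minority have received the recommended annual testing of metabolic markers". That sentence concerns all diagnosed Australians. Study cases are selected on HbA1c testing and may be better monitored; their lipid and albumin test counts are not given. This part of the objection stands.

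So does the point about size. Random timing and Poisson counts are assumptions, and care that follows an annual cycle is not random. The reversal in the lipid/albumin measure comes from cases moving from no or one test to two, and their share is unknown.

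Finally, no test at all is an issue for lipids and albumin only. An HbA1c case has at least one HbA1c test if the study period in the case definition means the 24-month period, which is the reading taken here.

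**Conclusion.** The concern holds as a fault in the outcome definition. Failure is counted only through between-test gaps, so cases with no or one lipid or albumin test, and cases never re-tested after an out-of-range result, cannot be counted as failing. This follows from the wording and needs no assumption.

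That more testing can raise measured failure is also certain for individual patients. Its size for a town is illustrative: 0% with no or one test against 21% with two, under random timing. It would be wrong to conclude that secondary aim 1 will be answered with the wrong sign. That depends on baseline test counts not in the article, and where most cases have several lipid or albumin tests the measure moves in the right direction.

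Only secondary aim 1 is touched; glycaemic control, the primary outcome, is not. This should be fixed before the post-test data are analysed.

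**What to change.** Keep every case in the denominator and apply one rule at baseline and post-test. Besides the between-test gaps already counted, count as failures:

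1. no lipid test, or no albumin test, in the 24 months;
2. a stretch from the last test to the end of the period that exceeds the stated limit;
3. an out-of-range result with no later test, leaving out results in the final four months.

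Count the stretch from the start of the period to the first test only for cases already seen in the data before or early in the period. Counting it for everyone would fail people newly diagnosed or newly arrived, whom the Discussion names as entering the data. If GP education raises detection, that could differ by arm. Counting it for everyone belongs in a sensitivity analysis. No data are extracted from before the baseline period, so the part of this condition that can be applied identically in both periods is a record of any test early in the period, with the cut-off fixed in advance.

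Report the number of tests per case in the 24 months beside the mean gap, which does not exist for cases with fewer than two tests. A rate per case-year would need entry and exit dates that are not listed for extraction.

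**Cost.** This is reprogramming from dates already extracted. Item 3 also needs result values; the extraction list names only dates for HDL cholesterol and urinary albumin, but the re-test measure as it stands needs those values too.

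**Limits.** Without death, relocation or diagnosis dates, some people who died or left are scored as failing, so the sensitivity analysis should check whether this differs by arm. For HbA1c cases whose start stretch is not counted, the reversal shrinks but does not vanish under random timing: one test fails with probability 17/24 = 71%, two with 2(17/24)² − (10/24)² = 83%. This is a further reason to show both versions and the test counts.

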##### Blood lipids and urinary albumin control

The following targets were recommended for blood lipids: total cholesterol <4.0mmol/L; triglycerides <1.5mmol/ L; HDL cholesterol >1.0 mmol/L; LDL cholesterol <2.5mmol/ L [13]. A urinary albumin excretion of <20 μg/min is considered normal [13]. Using the most recent results for each case within each 24-month timeframe, the mean values of blood lipids and urinary albumin and the proportion of all cases whose most recent values are within the relevant target ranges was determined.

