#### Secondary aims

To examine whether the above-mentioned intervention can:

1. Improve patterns of diabetes care as measured by whether the frequency of testing for hemoglobin A1c, blood lipids and urinary albumin meets NHMRC (National Health and Medical Research Council) guidelines.

2. Improve other clinical outcomes as measured by blood lipid control and urinary albumin control.

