### Selection of case sample

For the two-year baseline period, the two pathology companies used the postcode of the treating doctor to identify the potential cases in each study town. The existence of at least one HbA1c test was the criterion for an individual to be identified as a potential case of diabetes. A study case was defined by having either a single HbA1c test where the result was greater than 7%, or two HbA1c tests within the study period. This approach was used to exclude those cases where a single HbA1c test had been used to screen for diabetes. This criterion may have resulted in the omission of some cases of diabetes (*i.e.*, people with diabetes who had not had an HbA1c test). However, more serious forms of bias are avoided, because neither provider consent nor patient consent was required.

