### Measures

#### Primary outcome

##### Glycaemic control

The incidence and progression of complications of diabetes are reduced for people with lower HbA1c [8-10]. Therefore, guidelines recommend an overall target of ≤7.0% for HbA1c [6]. Using the most recent HbA1c for each case within each 24-month timeframe, the mean HbA1c across the town, and the proportion of all cases whose most recent HbA1c value is ≤7.0%, was determined.

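### Lipid and albumin control is a proportion of all HbA1c-defined cases, so, read literally, more testing alone raises apparent control

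*Protocol article*

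**What the plan says.** The control measure starts from one result per patient and window, "Using the most recent results for each case within each 24-month timeframe", and reports mean values together with "the proportion of all cases whose most recent values are within the relevant target ranges was determined" (Protocol article, Blood lipids and urinary albumin control).

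Who is a case is settled under Selection of case sample, by HbA1c alone: "A study case was defined by having either a single HbA1c test where the result was greater than 7%, or two HbA1c tests". No lipid or albumin test is needed. The article gives no rule for a case without a result for an analyte.

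The primary outcome has the same form: "the proportion of all cases whose most recent HbA1c value is ≤7.0%, was determined" (Glycaemic control).

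The secondary aims are listed separately. The first is "Improve patterns of diabetes care as measured by whether the frequency of testing for hemoglobin A1c, blood lipids and urinary albumin meets NHMRC" guidelines; the second is "Improve other clinical outcomes as measured by blood lipid control and urinary albumin control". The town-based feedback (Intervention group, item 3) covers testing frequency and target attainment for HbA1c and blood lipids. It does not name urinary albumin.

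**The concern.** For HbA1c, a denominator of all cases does no harm, because the case definition supplies a result (if cases are identified window by window). Applied to total cholesterol, triglycerides, HDL, LDL and urinary albumin, the same phrase gives a different quantity, because membership of the denominator no longer guarantees a value. A patient without a value is then indistinguishable from a patient out of target.

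The intervention is meant to change testing. If it succeeds on the first secondary aim, the proportion used for the second rises as well, even if nobody's lipids or albumin improve. A testing effect could then be reported as a clinical effect. The mean in the same sentence can come only from patients with a value, so under the literal reading the two summaries of one outcome describe different sets of patients.

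The planned testing outcomes do not fully expose this. Under Frequency of blood lipid and urinary albumin testing, the article counts gaps between tests and averages those gaps. A case with no test has no such gap, so no stated measure gives the share of cases without a result.

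**Working it through.** **1. The plan's own figure.** None is stated for lipid or albumin control. The Sample size section covers HbA1c control only: 50% v 60%, 80% power, 5% level. With a continuity correction this gives 408 per arm, as stated. The design effect is 1 + (464 − 1) × 0.015 = 7.945, and 2 × 408 × 7.945 = 6,483, against 6,490 stated. The figure reproduces but has no bearing on the denominator. Its cluster size and intraclass correlation are borrowed in step 4.

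**2. The identity.** For one analyte in one window, let t be the share of cases with at least one value and c the share in target among those cases. Read literally:

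- proportion over all cases = t × c
- difference between arms with c unchanged = (t1 − t0) × c
- difference among cases with a value = c − c = 0, provided newly tested patients have the same c

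**3. Size.** The article gives neither t nor c, so all values here are assumptions.

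| Share tested, t0 to t1 | c = 0.3 | c = 0.5 | c = 0.7 |
|---|---|---|---|
| 90% to 95% | +1.5 points | +2.5 | +3.5 |
| 80% to 90% | +3.0 | +5.0 | +7.0 |
| 60% to 75%, or 70% to 85% | +4.5 | +7.5 | +10.5 |

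For example, 0.75 × 0.7 − 0.60 × 0.7 = 0.525 − 0.420 = 10.5 points.

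**4. Chance that the artefact reaches significance.** The Statistical methods section compares town proportions by a two-sample t-test and treats secondary outcomes similarly. I took 464 cases per town, a two-sided 5% level and an intraclass correlation of 0.015. That correlation was estimated for HbA1c control, so its use here is a further assumption. The probabilities come from the noncentral t distribution.

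| Towns per arm | Testing difference | c = 0.3 | c = 0.5 | c = 0.7 |
|---|---|---|---|---|
| 7 | 15 points | 0.29–0.32 | 0.53–0.55 | 0.79 |
| 7 | 80% v 90% | 0.15 | 0.27 | 0.47 |
| 11 | 15 points | 0.44–0.48 | 0.75–0.77 | 0.95 |
| 11 | 80% v 90% | 0.22 | 0.41 | 0.68 |

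**5. The other denominator is not neutral either.** Let newly tested patients have in-target share c′. The proportion among cases with a value becomes [t0 × c + (t1 − t0) × c′] / t1. With t0 = 0.60, t1 = 0.75 and c = 0.5:

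- c′ = 0.7: (0.300 + 0.105) / 0.75 = 0.54, a shift of +4 points
- c′ = 0.3: (0.300 + 0.045) / 0.75 = 0.46, a shift of −4 points

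Again no patient's level has changed.

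**6. Data needed.** Under Data extraction procedure, total cholesterol, triglycerides and LDL are listed with date and value, but HDL cholesterol and urinary albumin with date only. From that list, neither version of the proportion, nor the mean, can be computed for those two.

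**The case against.** Five points can fairly be made on the other side.

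- **The rule is implied, not written.** A reader might infer that the plan deliberately scores an untested case as uncontrolled. It does not say so. The opening clause takes a result for granted, so the authors may have meant only cases with a value; the mismatch with the mean would then vanish. This stands as far as it goes. But the denominator that is written is all cases, and nothing in the article narrows it.
- **The size is assumed.** A reader might take the Background statement that "it appears that a minority have received the recommended annual testing of metabolic markers" as evidence of low testing here. It concerns recommended annual testing among Australians with diabetes. The relevant share is any result in 24 months among people already selected for HbA1c testing, a lower bar in a more-tested group. The article also expects modest effects from audit and feedback and allows for poor GP participation, so the small end of the range is quite possible. This stands. The 10-point difference called important belongs to HbA1c control and can serve only as a yardstick.
- **Feedback does not cover everything.** It names blood lipids but not albumin. For albumin, the link runs through the first secondary aim only. This stands.
- **Part of the safeguard exists.** Testing frequency and mean values are reported separately, so a testing effect without better levels might be noticed. This stands in part: neither shows how many cases had no value.
- **All cases is a legitimate denominator.** Tested and in target is a sensible population-level measure and keeps the randomised comparison. Restricting to tested patients conditions on something the intervention is meant to change. This stands, so a reader should not infer that a tested-only proportion ought simply to replace the all-cases one.

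**Conclusion.** The point holds as a flaw in how a secondary outcome is worded. Read literally, the control proportion is the product of testing and control, and a rise in testing moves it by (t1 − t0) × c with levels unchanged. Over testing rises of 5 to 15 points and c of 0.3 to 0.7, that is about +1.5 to +10.5 points. The range rests wholly on assumed t and c, and on newly tested patients having the same c as the others.

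The article does not support saying that a false gain of any particular size is expected, or that testing in these towns is known to be low. The primary outcome is not affected. What is supported is that, as the measures stand, a reader of the results could not separate better control from more testing. Separately, the extraction list and the control measure disagree on whether values exist for HDL cholesterol and urinary albumin.

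**What to change.** In the section on blood lipids and urinary albumin control:

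1. State the denominator for each analyte.
2. Report, by arm and by 24-month period, the share of cases with at least one value of that analyte.
3. Present control in two forms: among cases with a value, which is the population of the mean; and over all cases, labelled as tested and in target.
4. State that a claim of better control under the second secondary aim will not rest on the all-cases proportion alone.
5. Reconcile this section with Data extraction procedure for HDL cholesterol and urinary albumin, by confirming that values are extracted or by withdrawing the control measures for those two.

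Steps 1 to 4 need no new data for analytes whose values are already extracted. They cost a sentence or two and one more table row per analyte. Under Trial status the intervention phase is still nearing completion, so the wording can be fixed before post-test results exist. The downside is that the tested-only proportion can itself shift if newly tested patients differ, so neither form should be read without the share tested beside it.
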